**Inclusion criteria**
Age ≥ 65 years
Meet the diagnostic criteria of CHD, and the medical history ≥3 years
Visual and auditory discrimination is relatively intact, enough to cooperate with relevant tests
Voluntarily participate in the study and sign informed consent form
**Exclusion criteria**
Alzheimer's disease or other types of dementia
Patients with neurological and mental disorders, such as severe depression, schizophrenia, bipolar disorder, etc.
Have suffered from other diseases that affect cognitive function, such as cerebrovascular history, hypothyroidism, obvious folic acid and vitamin B12 deficiency, or previous intracranial surgery
Patients with severe heart disease and perioperative hemodynamic instability other than CHD, primary diseases with important organs, blood system or endocrine system
History of alcohol dependence and special drug abuse, including drugs^*^ that can cause cognitive changes
Patients with severe hepatic and renal insufficiency
Had been diagnosed with cognitive impairment or dementia before the first diagnosis of CHD
Participating in other clinical trials

* Drugs affecting cognitive function mainly include the following categories: anticholinergics, antiepileptics, antiparkinson's, antihistamines, tricyclic antidepressants, skeletal muscle relaxants.

### 2.3. Sampling and sample size

For the exploratory analysis of multiple risk factors, the sample size of this study is set to be >5–10 times the number of observed factors (16, 17). According to previous research reports, after 3.2 ± 0.37 years of follow-up, the incidence of cognitive impairment in patients with stable coronary heart disease is 42.4% (4). Clinical observations showed that patients with CHD had a relatively higher incidence of MCI. Based on the actual conditions of patients in the hospital, and the 18 independent variables pre-estimated in the study (detailed in the Outcomes Measures part), the sample range should be at least 90–180. Considering the absence and effectiveness of 5% of the samples, the total sample size finally determined by the two groups should ≥378. The final sample size of each group shall be determined according to the actual situation and can be adjusted appropriately.

### 2.4. Outcomes measures

Clinical, biological, social and environmental determinants of interest in this study were selected based on the potential or established association with cognitive impairment in patients with CHD and/or the fact that they are modifiable through preventive strategies.

#### 2.4.1. Demographic and clinical data

Standardized questionnaires will be used to collect demographic, symptom, and medical history data. Social demographic information includes age, gender, race, height, weight, BMI, marital status, education level, nature of work, and type of occupation. Clinical data include past and present diseases (acute and chronic), drugs, and family history of cardiovascular disease. Disease-related information includes the course of CHD, the results of coronary CT/ angiography, the number of coronary stents implanted, cardiac function class, the number of diseased vessels, types of statins, and drug treatment. Previous disease history and drug use also need to be recorded. Vital signs such as temperature, respiration, pulse and blood pressure are also covered.

#### 2.4.2. Cognitive assessment

At baseline, all participants underwent cognitive assessment. Global cognitive function will be assessed using the MoCA scale. Neuropsychological scale screening tests are crucial in the identification of cognitive impairment. Currently, the Mini-Mental State Examination (MMSE) and Montreal Cognitive Assessment (MoCA) are the most commonly used cognitive assessment tools. Of the two, MoCA covers a wider variety of cognitive domains than MMSE. In addition, meta-analysis findings (18) revealed that the sensitivity, specificity and AUC value of MoCA are higher than those of MMSE in elderly patients (over 60 years old) with MCI. Therefore, we choose MoCA as the screening method to determine whether there is MCI.

As a screening tool specially developed to detect MCI, it takes around 10 min to administer MoCA when executed (19). The MoCA covers 14 topics with a total of 30 points, including visual spatial structure skills, executive function, attention and concentration, short-term memory and delayed recall, language, abstract thinking, calculation and orientation. Due to varied geographies, cultures and populations, there are some differences in the cut-off values of MoCA screening for MCI among elderly individuals in various regions. Studies have shown that when using a cutpoint of 25/26, the MoCA has a sensitivity of 80–100% and specificity of 50 to 76% for detecting MCI (20). According to a survey to evaluate MCI in Beijing, China's urban and rural old communities, MoCA has excellent sensitivity and fairness specificity under the recommended critical score of 26 (21). The systematic review of MCI screening for the elderly in China also concurs that using a diagnostic threshold of 25/26 is the most practical option (22). Thus, the score of MoCA <26 is chosen as the benchmark to ascertain whether MCI exists in this study.

#### 2.4.3. Health and lifestyle

According to the investigation, researchers found that an insomnia history was associated with an increased risk of MCI, and a sleep disorder history may usefully predict MCI (23). Therefore, we specially selected the commonly used Pittsburgh Sleep Quality Index (PSQI) to analyze the sleep characteristics of the subjects. Sleep quality, falling asleep time, sleep time, sleep efficiency, sleep disorders, hypnotic drugs and daytime dysfunction are included in this scale. The World Health Organization (WHO) guidelines recommend that elderly people exercise at least 150 min medium intensity or 75 min high intensity aerobic exercise per week. So the physical activity of the participants will also be monitored to explore if it is related to MCI. Physical activity levels will be measured by using a Chinese version of the International Physical Activity Questionnaire-short form (IPAQ-S) (24).

#### 2.4.4. Laboratory indicators

Laboratory examination can accept the test results within 7 days before and after screening. It mainly includes the following contents: fasting glucose, glycosylated hemoglobin (HbA1c), total cholesterol, triglyceride, low-density lipoprotein, high-density lipoprotein, total bilirubin, serum creatinine, serum iron level (Fe), coagulation function (PT, APTT, TT, FIB), vascular ultrasound pulse wave velocity (PWV).

In addition to the above-mentioned indexes, in the early morning of the 2nd day after the selection, two tubes of peripheral venous blood of 5 ml will be drawn from a qualified phlebotomist and placed in the EDTA anticoagulant tubes. Centrifuge the blood samples (3,000 rpm at 4°C for 15 min), store them at −80°C, and then conduct untargeted metabolomics detection. 2 g of fresh fecal samples will be collected and put into aseptic collection tube and stored at −80°C immediately for metabolic detection and analysis of intestinal flora.

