### 2.6. Statistical analysis

Among the outcomes of this study, the measurement data in accordance with normal distribution are expressed by mean ± standard deviation, and independent sample *t*-test is used for comparison between the two groups. The measurement data that don't conform to the normal distribution are expressed in the median (quartile), and the Mann-Whitney U test is used for comparison between the two groups. Counting data were expressed as frequency or percentage, and X^2^ test was used to compare the two groups. Single factor analysis shall be conducted for all factors. In order to avoid the omission of important variables, the covariates with P <0.1 in the univariate analysis will be included in the multivariate logistic regression analysis. Stepwise forward regression analysis is used to analyze the independent risk factors of cognitive impairment in patients with CHD, and the OR value and 95% CI of each related factor will be estimated. The risk prediction model of cognitive impairment in patients with CHD would be established by adding independent risk factors. ROC curve will be drawn and the area under the curve (AUC) will be calculated to evaluate the effectiveness of the prediction model. Use Bootstrapping method to verify the accuracy of the final model internally. All tests with P<0.05 on both sides indicate that the difference is statistically significant, and other statistical analysis can be carried out by SPSS25.0.

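### Treatment-sensitive laboratory values are screened unadjusted and selected stepwise, with no rule that keeps the matching treatment beside them

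*Protocol article*

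**What the plan says.** Protocol article, section 2.4.4 lists among its indicators "fasting glucose, glycosylated hemoglobin (HbA1c), total cholesterol, triglyceride, low-density lipoprotein, high-density lipoprotein" and "coagulation function (PT, APTT, TT, FIB"). It does not refer to treatment at the time of sampling.

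Section 2.4.1 does collect treatment. Its disease-related items end with "the number of diseased vessels, types of statins, and drug treatment", and it adds: "Previous disease history and drug use also need to be recorded".

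Section 2.6 then fixes the route from indicator to conclusion:

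- Each candidate is first tested alone: "Single factor analysis shall be conducted for all factors".
- The entry rule follows: "the covariates with P <0.1 in the univariate analysis will be included in the multivariate logistic regression analysis".
- Selection among those that entered is automatic: "Stepwise forward regression analysis is used to analyze the independent risk factors of cognitive impairment in patients with CHD".

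The two-group comparison uses the t-test for normally distributed measurements and Mann-Whitney otherwise. No variable is forced into the model, and no laboratory value is tied to, or stratified by, the treatment that moves it.

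**The concern.** Table 1 requires a CHD history of at least 3 years. Its list of excluded drug classes does not contain lipid-lowering, glucose-lowering or anticoagulant drugs. Treated patients are therefore to be expected, although the article does not say how many.

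In such patients some laboratory values partly measure the treatment. Two errors follow, in opposite directions:

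- **False selection.** PT, APTT and TT in an anticoagulated patient reflect the anticoagulant, and so its indication. If the indication is related to cognition, PT differs between the groups with no effect of its own. Forward selection may then take PT and leave the drug out.
- **Missed effect.** On-treatment LDL mixes the patient's lipid exposure with the strength of treatment, which weakens a real association. The screen at P<0.1 is univariate, so LDL can be discarded before any drug variable has had a chance to adjust it. Section 2.6 gives avoiding the omission of important variables as its reason for the 0.1 threshold, and the Introduction names hyperlipidemia and diabetes as risk factors.

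What is at stake is the list of independent risk factors. Section 2.4 chooses determinants partly because they can be modified, so it matters whether a listed factor is the laboratory value or its treatment.

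**Working it through.** **1. Sample size used.** Section 2.3 gives 18 variables and a multiple of 5–10: 18 × 5 = 90 and 18 × 10 = 180. The stated 378 follows as 180 × 2 groups = 360, then 360 × 1.05 = 378. The doubling is inferred. The checks use n=360 (step 4: n=378) and the 42.4% impairment figure of section 2.3. All other inputs below are assumptions.

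**2. Is the drug a candidate?** Section 2.6 sends all factors through the screen, so on a literal reading it is. But section 2.4.4 lists 14 values, and section 2.4.1 lists 10 demographic and 7 disease or treatment items: 14 + 10 + 7 = 31, before lifestyle. The 18 variables cannot hold them all and are not itemised. Both cases are therefore shown.

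**3. PT with no effect of its own.** Assumed: PT 12 ± 0.9 s untreated and 21 ± 5 s on an anticoagulant, 10% treated, indication OR for impairment 2. This mixture is clearly non-normal, so section 2.6 calls for Mann-Whitney. Stepwise entry is at P<0.05.

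| Outcome for null PT | Base case | Over 5–15% treated, OR 1.5–2.5 | Nominal |
|---|---|---|---|
| Passes univariate P<0.1 | about 26% | about 12–53% | 10% |
| Retained, drug a candidate | about 8% | about 3–14% | about 5% |
| Retained, drug not a candidate | about 18% | about 4–50% | about 5% |
| Passes P<0.1, only patients not on anticoagulants | about 10% | – | 10% |

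Base-case excess: 26 − 10 = 16 percentage points at the screen. After selection it is 8 − 5 = 3 points with the drug a candidate and 18 − 5 = 13 without it.

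**4. The same mechanism in general form.** Null laboratory value, n=378, drug use 20% or 50%, drug or indication OR 1.5 or 2.0, shift of 1 or 2 SD, 2,000 runs per scenario, selection at P<0.05:

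- drug absent from the analysis: 8.6% to 63.8%
- drug a candidate under the section 2.6 algorithm: 4.2% to 10.1%
- drug forced in beside the value: about 5.0% to 5.4%

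In the middle case, nearly every selection of the null value is one where it entered in place of its drug.

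**5. LDL with a real effect.** Assumed: untreated LDL 3.5 ± 0.9, true OR 1.30 per SD of untreated LDL. Of the patients, 10% are untreated, 50% have a 30% reduction and 40% a 50% reduction. On-treatment LDL = untreated × (1 − reduction) × lognormal noise (SD 0.12).

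| | Intensity unrelated to LDL | Intensity follows LDL |
|---|---|---|
| OR per SD, on-treatment LDL alone | 1.20 | 1.14 |
| OR per SD, with treatment category | 1.34 | 1.20 |
| Passes P<0.1, on-treatment LDL alone | 50% | 34% |
| Passes P<0.1, with treatment category | 68% | 47% |

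Untreated LDL, if it could be observed, would pass in about 77%. Adjustment gains 68 − 50 = 18 and 47 − 34 = 13 points, and still falls short of 77% by 9 and 30 points. The ORs are per SD of different variables, so the pass rates are the fairer comparison.

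**The case against.** The strongest reply is that treatment is in the plan. Section 2.4.1 records it and section 2.6 tests all factors, so the drug can compete with its laboratory value. This stands. A reader might infer that these values are analysed with no regard to the drug, but the text does not support that. With the drug as a candidate, the excess false selection is a few percentage points in most scenarios. Two limits remain: candidacy is not assured (18 variables against at least 31 listed items), and it does nothing for LDL, which is judged alone at the screen.

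A reader might also infer that treatment effects will be reported as biology. That goes too far. It is a risk, and the Discussion restricts conclusions to association.

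A t-test on the same PT inputs gives about 51% at P<0.1 and 39% at P<0.05. Those figures do not apply, because section 2.6 prescribes Mann-Whitney for data of this shape.

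For pure prediction, an on-treatment value is a legitimate predictor, since it is what the clinician sees. This stands, and it confines the point to the risk-factor aim.

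Table 1 also excludes severe heart disease other than CHD and primary endocrine disease. Read strictly, this could thin out anticoagulated or diabetic patients and shrink those parts of the problem. The article does not settle it.

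Finally, coding of statin intensity and filtering of drug-derived metabolites are details that an article may leave to the full protocol, so they are not part of this point. The selection algorithm is different: section 2.6 states it.

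**Conclusion.** The point holds in a limited form. The stated algorithm does not keep treatment beside the laboratory values it affects, so a value can be named an independent risk factor in place of its drug or indication, and a real lipid effect can be dropped at the first step.

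For PT the harm after selection is small if anticoagulant use is a candidate and material if it is not. For LDL the loss at the screen is moderate, and the drug's candidacy does not prevent it. Adjustment reduces that loss without removing it.

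The sizes rest on assumed treatment frequencies, indication ORs, drug shifts and LDL reductions, none of which the article gives. The direction follows from section 2.6 itself, provided that treated patients are enrolled.

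**What to change.** In section 2.6, for the risk-factor analysis:

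- Whenever lipids or glucose/HbA1c are tested or entered, including at the P<0.1 screen, keep the matching treatment variable (lipid-lowering or glucose-lowering) in the same model and exempt it from stepwise removal.
- Compare PT, APTT and TT in patients not on anticoagulants, or force anticoagulant use into the model.
- State that these treatment variables are among the candidates counted in section 2.3.

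On-treatment values may remain as predictors in the pure prediction model.

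The cost is analysis wording, a few degrees of freedom and slightly fewer patients in the coagulation comparison. Drug use is already collected. The LDL gain shown above assumes a three-level treatment category; a plain yes/no variable should be expected to recover less.

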### 2.5. Quality control

All researchers can enter and conduct this trial only after they have completed the training and obtained the authorization of the principal researcher. The involved researchers were trained in Good Clinical Practice (GCP) prior to the start of this study. Every researcher has received training in research procedure and plan. Including the collection of the MoCA scale, the researchers mastered the relevant questioning skills and evaluation criteria after strict and standardized training in advance. Ensure the rigor and consistency of the implementation process. All investigators have a thorough understanding of the information in this clinical research protocol, master the GCP principles, unify the recording methods and judgment standards, and strictly follow the protocol.

### 2.6. Statistical analysis

Among the outcomes of this study, the measurement data in accordance with normal distribution are expressed by mean ± standard deviation, and independent sample *t*-test is used for comparison between the two groups. The measurement data that don't conform to the normal distribution are expressed in the median (quartile), and the Mann-Whitney U test is used for comparison between the two groups. Counting data were expressed as frequency or percentage, and X^2^ test was used to compare the two groups. Single factor analysis shall be conducted for all factors. In order to avoid the omission of important variables, the covariates with P <0.1 in the univariate analysis will be included in the multivariate logistic regression analysis. Stepwise forward regression analysis is used to analyze the independent risk factors of cognitive impairment in patients with CHD, and the OR value and 95% CI of each related factor will be estimated. The risk prediction model of cognitive impairment in patients with CHD would be established by adding independent risk factors. ROC curve will be drawn and the area under the curve (AUC) will be calculated to evaluate the effectiveness of the prediction model. Use Bootstrapping method to verify the accuracy of the final model internally. All tests with P<0.05 on both sides indicate that the difference is statistically significant, and other statistical analysis can be carried out by SPSS25.0.

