**Methods:**

The cross-sectional study design will recruit 378 patients with CHD (≥65 years) from Xiyuan Hospital of China Academy of Chinese Medical Sciences. The subjects' cognitive function is evaluated with MoCA scale, and they are divided into cognitive impairment group and normal cognitive function group according to the score results. Demographic data, disease characteristics (results of coronary CT/ angiography, number of stents implanted, status of diseased vessels), laboratory tests (biochemistry, coagulation, serum iron levels, pulse wave velocity), metabolites (blood samples and intestinal metabolites), and lifestyle (smoking, alcohol consumption, sleep, physical activity) will be assessed as outcome indicators. Compare the two groups and the correlation analysis will be performed on the development of mild cognitive impairment. Mann-Whitney U or X^2^ test was selected to describe and evaluate the variation, and logistics regression analysis was employed to fit the prediction model. After that, do the calibration curve and decision curve to evaluate the model. The prediction model will be validated by a validation set.

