## 3. Discussion

Age-related cognitive decline is a series of natural cognitive changes that may develop into MCI or dementia. MCI is a state of cognitive impairment between healthy aging and dementia, which is considered as the prophase of dementia (25). But at this stage, the function of daily life remains basically intact. Delaying the onset of cognitive decline is the optimal strategy but where there are some earlier measures to slow the decline is important. Through comparative analysis of the population characteristics of the two groups, our study will screen out the specific markers of cognitive impairment in patients with CHD. So as to provide reference for early clinical identification and intervention of the disease.

The objective of this study is to ascertain the relationship between CHD and its risk factors and cognitive impairment in the elderly. At the same time, establish the risk prediction model of cognitive impairment in patients with CHD. The study will make available data regards CHD and MCI risk prediction. We propose leveraging the progress of machine learning to systematically compare different modeling approaches (26) to develop predictive tools for cognitive impairment in patients with CHD and verify their effectiveness. Comprehensive application of clinical observation, multi-source data processing, machine learning and other methods is also the innovation of the study.

Still, this research is subject to certain limitations. As an observational study, cross-sectional design has limitations e.g., causality cannot be inferred, we can only address the association. However, we try to include more observation factors, which are widely related to basic demographic data, disease characteristics, blood chemistry, metabolites and lifestyle. It is expected that some risk factors with clinical value can be found on the basis of this exploratory analysis. In order to broaden the current knowledge on CHD and its relationship with cognitive impairment in the elderly. Additionally, it will serve as a valuable foundation for hypothesis generation for future longitudinal studies and / or randomized controlled trials. In the future, it is necessary to conduct a larger sample of prospective cohort studies and add follow-up time to determine the incidence of secondary MCI in patients with CHD.

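### The bootstrap is specified for the final model after data-driven selection, so on a literal reading part of the selection optimism stays in the reported AUC and calibration; separately, the Abstract names a different validation scheme

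*Protocol article*

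**What the plan says.** Section 2.6 (Statistical analysis) sets out the model building in this order:

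1. Every factor is tested singly, and "the covariates with P <0.1 in the univariate analysis will be included in the multivariate logistic regression analysis".
2. "Stepwise forward regression analysis is used to analyze the independent risk factors of cognitive impairment in patients with CHD". No entry level is given for this step.
3. "The risk prediction model of cognitive impairment in patients with CHD would be established by adding independent risk factors".
4. "ROC curve will be drawn and the area under the curve (AUC) will be calculated to evaluate the effectiveness of the prediction model".
5. "Use Bootstrapping method to verify the accuracy of the final model internally".

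The Abstract (Methods) describes the assessment differently: "After that, do the calibration curve and decision curve to evaluate the model", followed by "The prediction model will be validated by a validation set". Section 2.6 mentions neither a validation set nor these two curves.

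The Discussion adds that the team proposes to use machine learning to "systematically compare different modeling approaches". Section 2.6 does not cover this.

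Section 2.3 counts 18 independent variables, cites a 42.4% frequency of cognitive impairment, and arrives at a total of at least 378. Section 2.4.4 adds untargeted metabolomics without giving a number of features.

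**The concern.** When predictors are chosen on the same data that estimate the model, performance is overstated for two reasons: the coefficients are fitted to noise, and the variables themselves are partly chosen because of noise. A bootstrap that refits only the already chosen variables measures the first and misses the second. To measure both, each resample has to go through the whole sequence from the first screen onwards.

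The prediction model is a main deliverable, meant to support early identification and intervention. An AUC that is somewhat high matters for comparison with other models. A calibration slope reported close to 1 when the true slope is clearly lower matters more, because the predicted risks are then too extreme while appearing sound.

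The second issue is separate. The article names two different validation designs, and nothing says which one counts. They differ in what they estimate, in precision and in the patients they need.

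**Working it through.** **The plan's sample size.** 18 variables × 10 = 180; × 2 groups = 360; × 1.05 = 378. The doubling is inferred, since section 2.3 gives 90–180 and then a total for both groups, but it reproduces 378 exactly. No term is left over for a validation set. Expected events: 0.424 × 360 ≈ 153, or 153/18 = 8.5 per candidate.

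**Size of the uncorrected optimism.** The article gives no performance figure to reproduce, so the size was simulated. For each dataset:

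- apparent AUC: the selected model scored on its own data;
- bootstrap-corrected AUC = apparent AUC − mean over resamples of (AUC of the resample's model in the resample − AUC of that model in the original data), once with the selected variables held fixed and once with screen and selection repeated;
- true AUC: the selected model scored on 20,000 new subjects.

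Both simulations used the P<0.1 screen from section 2.6, then forward entry at 0.05 (assumed), with about 42% events.

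- Simulation A: n = 359, predictors correlated 0.1, five real predictors at log-odds 0.3 per SD, 120 datasets × 40 resamples.
- Simulation B: n = 360, independent predictors, five real at 0.40, 0.30, 0.25, 0.20 and 0.15 per SD, 80 datasets × 60 resamples (40 × 40 for 100 candidates).

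| Setting | Apparent | Fixed-variable bootstrap | Selection repeated | True | Excess left by fixed | Share of optimism removed by fixed |
|---|---|---|---|---|---|---|
| A, 18 candidates | 0.702 | 0.690 | 0.663 | 0.671 | 0.019 | 0.012/0.031 = 39% |
| B, 18 candidates | 0.668 | 0.655 | 0.616 | 0.623 | 0.032 | 0.013/0.045 = 29% |
| A, 40 candidates | 0.71 | 0.70 | 0.65 | 0.67 | 0.03 | 0.01/0.04 = 25% |
| B, 40 candidates | 0.688 | 0.672 | 0.610 | 0.613 | 0.059 | 0.016/0.075 = 21% |
| B, 100 candidates | 0.726 | 0.702 | 0.604 | 0.596 | 0.106 | 0.024/0.130 = 18% |
| B, 18 candidates, none real* | 0.586 | 0.581 | 0.524 | 0.499 | 0.082 | 0.005/0.087 = 6% |

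*Only datasets in which something was selected: 80 of 118.

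Calibration slope (1 is ideal):

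| Setting | Fixed-variable bootstrap | Selection repeated | True |
|---|---|---|---|
| A, 18 candidates | 0.94 | not available | 0.83 |
| B, 18 candidates | 0.94 | 0.71 | 0.73 |
| A, 40 candidates | 0.93 | not available | 0.75 |
| B, 40 candidates | 0.92 | 0.63 | 0.58 |
| B, 100 candidates | 0.87 | 0.50 | 0.38 |

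The rows with 18 candidates use the plan's own count. The others show what happens if more is screened. Section 2.6 tests all factors, and sections 2.4.1 to 2.4.4 list roughly 40 items by my count, before any metabolites.

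**The two validation statements side by side.** Section 2.6 has an internal bootstrap and no validation set. The Abstract has a validation set and no bootstrap. Section 2.3 reserves no patients. Section 2.1 allows for further hospital sites but does not link them to validation. If the set were split from the planned patients, 70/30 for illustration, 153 events would become about 107 for training and 46 for validation. The 95% interval for an AUC of 0.70 would be about ±0.10, against about ±0.06 on all patients (Hanley–McNeil).

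**The case against.** **The text does not say the variables are held fixed.** Naming the final model as the thing being verified is compatible with a bootstrap that repeats selection, and a condensed article may leave resampling steps to a fuller document. This stands in part: the bias is conditional on the literal reading. But section 2.6 places the bootstrap after selection and attaches it to the final model, and an analyst following it would most naturally refit the chosen variables.

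**The bias is small at 18 candidates.** An excess of 0.019 to 0.032 is a third to a half of the ±0.06 sampling error. That is fair for the AUC, although the bias always goes one way. It is less fair for the calibration slope.

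**The study is exploratory.** The Discussion says so and foresees larger cohorts. This lowers the urgency.

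Several stronger readings are tempting but not supported:

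- *That the Abstract's validation set adds to the optimism.* A truly separate set would give an unbiased AUC.
- *That bootstrapping the final model corrects almost nothing.* With real predictors and 18 candidates it removes 29% to 39% of the AUC optimism.
- *That a worthless model would look validated.* With no real predictor among 18, the fixed-variable bootstrap gives an AUC of about 0.58, which few would take as validation. The introduction also describes several candidates as established risk factors.
- *That a validation set could only come out of the 378.* The total is a minimum and sites may be added. What holds is that none is provided for.
- *That the model will be judged by AUC alone.* The Abstract plans calibration and decision curves, and section 2.6 does not exclude them.

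**Conclusion.** The point holds in two separate parts.

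First, section 2.6 read literally leaves part of the selection optimism in the reported performance. At the plan's 18 candidates the AUC is about 0.02 to 0.03 too high, and the calibration slope is reported as about 0.94 against a true 0.73 to 0.83. In simulation B the AUC excess rises to about 0.06 with 40 candidates and 0.11 with 100. The direction is the same in every setting tried. The size rests on assumed effects, normal predictors with little or no correlation, and an assumed 0.05 entry level. If a fuller protocol already repeats selection within resamples, most of this bias disappears.

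Second, the Abstract and section 2.6 name different validation schemes, and the sample size makes no provision for the one in the Abstract. This inconsistency stands whichever way the bootstrap is run.

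This should be fixed before analysis. It is not a fatal flaw in an exploratory study.

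**What to change.** State one validation scheme, in the same terms, in the Abstract and in section 2.6:

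- Develop the model on all patients.
- In each bootstrap resample (for example at least 500), repeat the P<0.1 screen, the stepwise selection and, if models are compared, the choice among machine-learning approaches. State the stepwise entry level.
- Report optimism-corrected AUC, calibration slope and intercept, and draw the calibration curve from the optimism-corrected model. Name the calibration and decision curves in section 2.6.
- Keep the validation-set sentence only if its source, such as an added site, and its size are stated. Otherwise delete it.

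The cost is a few sentences and some scripting, with no new data. The reported AUC will be slightly lower. The correction is not exact: repeating selection came within about 0.01 of the true AUC in simulation B with real predictors, but fell 0.02 below it in simulation A with 40 candidates. Its slope was still somewhat high with 40 and 100 candidates. It was nonetheless closer to the truth than the fixed-variable bootstrap in every setting tried.
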